#### 8.4.2 Informed Consent Procedures

We will use the Western Institutional Review Board (WIRB) as the IRB of record for the study and comply with all necessary requirements at each site. Each site will use the IRB-approved (1) Informed Consent and (2) Research Authorization or HIPAA disclosure form allowing study access to protected health information in the patient's ED medical record. Because of the time constraints of completing the assessment and intervention in the ED, the informed consent form will be as brief as possible within the constraints of adequate human subjects' protections. These documents will include a description of the following key elements including: the assessment interview and questionnaires; the follow-up interviews; risks and benefits of the buprenorphine formulations being offered and study procedures; alternatives to participation in the study; confidentiality; payment for participation; a statement that participation is voluntary and that they may freely withdraw participation at any time; and information about whom to contact with questions or in case of emergency. The Informed Consent includes assurances of confidentiality (including a Certificate of Confidentiality) and that the decision to participate will in no way influence other aspects of the patient's treatment.

In addition, potential participants will be instructed concerning the importance of full and accurate disclosure and that compensation and continuation in the study has nothing to do with their drug

use or test results. Initial screening questions will be asked with verbal consent however, all eligible study patients will be asked for written consent to participate using the IRB-approved forms.

Given the multisite nature of the trial, it is possible that additional studies will be proposed before or after the study begins recruitment. For this reason, during the informed consent process, we also will seek permission to contact the participant in the future about other study opportunities. Staff will be available to answer questions about the consent form while participants are reviewing it.

#### 8.4.3 Eligibility Confirmation, Enrollment Randomization

Once the study eligibility is confirmed and both consent forms are signed, the patient will be considered enrolled in the study. The enrollment procedures will be captured through a centralized process managed by the CTN Data and Statistics Center (DSC). Study patients who do not complete all screening assessments or who are otherwise found to be ineligible for participation in the study will be considered screen failures. Section 8.5 describes all study assessments.

#### 8.4.4 Randomization Procedures

Eligible participants will be randomized in a 1:1 ratio to XR-BUP or SL-BUP. The randomization process will be performed by computer by the DSC. A permuted block randomization procedure with random block sizes will be implemented to balance on site and insurance status (public, private, none).

The randomization procedure will be conducted centrally through the DSC. The DSC statistician will generate the randomization schedule using balanced blocks of varying sizes within strata to ensure lack of predictability along with relative equality of assignment across treatment groups. The DSC statistician will review randomization data on a regular basis to ensure that the scheme is being implemented according to plan. A randomization slot, once used, will not be re-allocated.

#### 8.4.5 Participant Withdrawal from the Study

All participants will be followed for the duration of the study (CTN-0099) unless they withdraw consent, die, or the investigator or sponsor decides to discontinue their enrollment for any reason. Reasons for the investigator or sponsor terminating a participant from the study may include, but are not limited to, the participant becoming a threat to self or others, lack of funding, or DSMB early termination of the study for safety or effectiveness reasons. At any time, participants may decide that they no longer wish to continue to participate in the study.

#### 8.4.6 7-day Follow-up Assessments

Follow-up assessments are expected to be conducted at 7 days post enrollment via telephone by the ED study staff. Assessment of engagement in formal addiction treatment on the 7th day after enrollment will be based on direct contact with the treatment provider/program provided by the

participant and or referral noted in the EHR. Printed reminders for the follow-up assessment will be given to the study participant prior to ED discharge. In addition, the RA will send a reminder in the mail/text/email/or social media (based on study participant preference) about 3 days prior to the scheduled follow-up with an additional reminder notification via mail/text/email/or social media (based on study participant preference) the day before the scheduled follow-up.

#### 8.4.7 30-day Follow-up Assessments

Follow-up assessments are expected to be conducted at 30-days post enrollment via telephone by the ED study staff. Assessment of engagement in formal addiction treatment on the 30th day after enrollment will be based on direct contact with the treatment provider/program provided by the participant. Printed reminders for the follow-up will be given to the study participant prior to discharge. In addition, the RA will send a reminder in the mail/text/email/or social media (based on study participant preference) about 7 days prior to the scheduled follow-up with an additional reminder phone call the day before the scheduled follow-up.

#### 8.4.8 Compensation

Because of the expected difficulty of maintaining high follow-up rates in the study population, adequate compensation for time and inconvenience is critical. Compensation of a \$50 gift card will be distributed in-person for completing the enrollment process at the initial ED visit, and a \$50 gift card for the 7 and 30-day follow-up assessments will be mailed or available for pickup based on patient's preference for a total of \$150 at study completion. Compensation will be in accordance with the IRB of record's policies and procedures, and subject to IRB approval.

#### 8.4.9 Interventions: Buprenorphine Induction and Discharge Instructions

Uniform BUP induction protocols will be used:

a) Standard SL-BUP:

- i. COWS  $\geq 8$ : Patients will receive 4mg of SL-BUP for a COWS score of 8-12 (mild withdrawal). After 30-45 minutes if tolerated and no unanticipated adverse reactions, an additional 4mg can be administered for a total of 8mg in the ED. Patients presenting with moderate-severe withdrawal ( $\text{COWS} \geq 13$ ) will receive an initial dose of 8mg SL-BUP. All patients will receive a buprenorphine prescription and instructions for additional BUP doses to allow for up to a dose of 12mg if needed, and for 16mg each subsequent day until their scheduled follow up appointment for ongoing MOUD.
- ii. COWS 4-7: Patients will be provided with a uniform set of instructions to guide unobserved (home) induction. They will be prescribed doses of SL-BUP to allow them to take dose up to 12mg in the 24 hours after discharge. All patients will also receive a buprenorphine prescription for 16mg each subsequent day until their scheduled follow up appointment for ongoing MOUD.

b) XR-BUP Injection with CAM2038 24 mg: Based on published data for equivalency of 16mg of SL-BUP and experience with the phase 3 trial, patients will receive a 24mg dose of injectable CAM2038 in the ED on Day 0. The patient will remain in the ED for 2-hours post injection to observe for worsening withdrawal or precipitated withdrawal as defined below in Section 9.8.

- i. SL-BUP Rescue Dose: If patient's COWS score is  $> 12$  after XR-BUP injection, a 4-8 mg dose of SL-BUP can be administered.

Patients can receive any of the ancillary medications per standard of care for specific symptoms of withdrawal. Example includes ondansetron for nausea or acetaminophen for headache.

Discharge Instruction: Participants randomized to XR-BUP will receive a wallet card with instructions for signs and symptoms of precipitated withdrawal and advice to return to the ED for immediate evaluation for the first 24 hours post dosing if precipitated withdrawal is suspected. Each ED will have a clinician on call for the study to assist in assessment and treatment.

#### 8.4.10 Worsening or no improvement in Withdrawal Symptoms

- XR-BUP: Additional doses of 2-16 mg of SL-BUP may be given to participants whose COWS score increases to  $> 12$  within 2 hours of XR-BUP injection.
- SL-BUP: If patients continue to have a COWS score  $> 12$  after the initial 8mg, they can receive additional doses of SL-BUP

(Note: patients may receive ancillary medications per standard of care for the treatment of the specific withdrawal symptoms prior to or after additional SL-BUP. For example, ondansetron for nausea.)

- If patients continue to have withdrawal symptoms  $> 12$  in either group after additional SL-BUP, they can receive ancillary medications:

- **For muscle aches and pains:** Acetaminophen 650 mg, NSAIDs: Ibuprofen 200-800 mg; ketorolac 30-60 mg
- **For abdominal cramps and diarrhea:** Dicyclomine (Bentyl) 20 mg, Loperimide (Imodium) 2 mg
- **For nausea:** Ondansetron (Zofran) 8 mg, Prochlorperazine (Compazine) 5-10 mg, OR promethazine (Phenergan) 12.5-25 mg
- **For elevated blood pressure, tachycardia or anxiety/restlessness:** Clonidine 0.1-0.3 mg, q 4-6 hrs, not to exceed 0.6 mg in 24 hrs, (hold for systolic blood pressure < 100 mmHg, or heart rate < 56 bpm)

#### 8.4.11 Precipitated Withdrawal with XR-BUP

Clinicians will assess patients whose COWS increases to > 12 within 1 hour of administration and determine if the event is considered a precipitated withdrawal. This clinical determination will be based on the severity of the withdrawal signs and symptoms, the rapidity of the onset of withdrawal symptoms, and clinical factors (e.g., timing since last use of an opioid agonist(s), type(s) of opioid agonist, duration of action of opioid agonist(s) used, and route of administration). Scores will be based on objective components, eliminating nausea which can be a side effect of the BUP administration.

Patients who experience precipitated withdrawal will be treated with ancillary medications as described above. We will collect information that may predispose participants to precipitated withdrawal on all participants. This will include recent exposure to buprenorphine, fentanyl, and other opioids via urine testing and self-report, and receipt of naloxone in the ED or pre-hospital setting. This information will be collected on the Precipitated Withdrawal form (PWD), Urine Drug Screen (UDS) form and the Timeline Followback Supplement (TFS) form, which is a supplement to the Timeline Followback that solicits substance use for 24 hours prior to enrollment.

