We have demonstrated that approximately 50% of patients with untreated OUD in the ED are not eligible for initiation (induction) of buprenorphine at the time of their ED visit due to insufficient severity of opioid withdrawal. In order not to miss this important and substantial patient population, it is imperative to investigate strategies for ED-based initiation of BUP. Our work, and others, demonstrates the safety and efficacy of unobserved (e.g., home) BUP induction in patients, including those in the ED, with low withdrawal severity. As the pharmacology of XR-BUP, in contrast to SL-BUP, has a slower onset of activity at the mu opioid receptor, it lends itself to direct induction in individuals with low COWS scores (COWS < 8) from the ED. The median time to peak concentration is 24 hours versus about 2.5 hours for SL-BUP. However, serum concentrations of buprenorphine with XR-BUP are rapidly detectable which likely results in adequate BUP to provide adequate relief of withdrawal. Thus, we will conduct a small ancillary study of approximately 75 patients in approximately 4-10 sites with ED clinicians who have experience with BUP inductions. This ancillary study will inform the larger pragmatic trial and potentially expand recruitment in the Effectiveness RCT component to include ED patients with COWS <8. The goal will be to allow expansion of the Effectiveness RCT to ED patients with COWS <8 allowing for randomization in this group of patients to ED initiated XR-BUP vs.

unobserved induction with a prescription for SL-BUP (See Potential modifications to Effectiveness RCT based on Ancillary Study Component below).

It is advantageous to develop electronic health record (EHR) phenotypes of opioid-related illnesses that accurately and automatically characterize ED visits, enhance active disease surveillance, and better identify patients potentially eligible for study inclusion, increasing the generalizability of trial findings. Thus, we include an EHR phenotype development and validation aim that will aid the proposed current and future opioid-related research trials in EDs.

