### 8.9.4 Adverse Events (AEs) and Serious Adverse Events (SAEs)

Adverse events will be captured and reported through the Adverse Event (AE) reporting mechanisms described in Section 18. Events including withdrawal (except for precipitated withdrawal), injection site reactions, assessments for suicide risk, overdose and vital signs do not need to be reported as Adverse Events and will be captured on specific study forms. If any of these events meet the definition of a SAE described in Section 18, then they would be reported on the AE/SAE forms set.

The reporting period for AEs and SAEs for the RCT starts at XR-BUP administration and ends at the last study visit, day 30 after enrollment.

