### 9.8 Precipitated Withdrawal

Clinicians will assess patients whose COWS increases to > 12 during the 4 hours of observation post administration and determine if the event is considered a precipitated withdrawal. This clinical determination will be based on the severity of the withdrawal signs and symptoms, the rapidity of the onset of withdrawal symptoms, and clinical factors (e.g., timing since last use of an opioid agonist(s), type(s) of opioid agonist, duration of action of opioid agonist(s) used, and route of administration). Scores will be based on objective components, eliminating nausea which can be a side effect of the BUP administration.

Patients who experience precipitated withdrawal will be treated with ancillary medications as described above.

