##### **14.24.1 Adverse Events and Serious Adverse Events**

Adverse events will be captured and reported through the Adverse Event reporting mechanisms described in Section 18.0.

Events including withdrawal, injection site reactions, assessments for suicide risk, overdose and vital signs do not need to be reported as Adverse Events and will be captured on specific study forms. If any of these events meet the definition of a Serious Adverse Event described in Section 18.0, then they would be reported on an AE/SAE form set.

The reporting period for the randomized controlled trial begins at study product administration and ends at the last study visit, day 30 after the study injection, and the reporting period for the ancillary study begins at study product administration and ends at day 7.

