#### **8.2.4 Precipitated Withdrawals**

A table summarizing the number of participants experiencing a precipitated withdrawal as well as the number of such withdrawals will be generated by treatment arm. A listing of precipitated withdrawals will be provided.

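### The RCT gives conflicting windows for assessing precipitated withdrawal after XR-BUP, is ambiguous for patients entering with COWS above 12, and names no window for the pausing count or the safety table

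*Combined protocol and SAP*

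**What the plan says.** **Window.** The RCT's own section, 8.4.11, reads: "Clinicians will assess patients whose COWS increases to > 12 within 1 hour of administration", and has them decide whether the event is precipitated withdrawal. Section 8.4.9 keeps XR-BUP patients in the ED for 2 hours to "observe for worsening withdrawal or precipitated withdrawal as defined below in Section 9.8". Section 9.8 is in the ancillary component and reads: "Clinicians will assess patients whose COWS increases to > 12 during the 4 hours of observation post administration". Section 8.9.3 confirms that RCT observation lasts 2 hours.

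**Who enters.** RCT inclusion (8.3.1) sets only a lower bound, COWS of at least 4. Section 8.4.9 has an SL-BUP branch for patients presenting at 13 or more, so such entrants are expected.

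**Form and count.** Section 8.9.2 describes a form that records whether the event occurred and when. The determination rests on severity, speed of onset and clinical factors, with no COWS threshold and no time limit. The pausing rules in 8.4.12 count precipitated withdrawals overall and by site, also without a window.

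**Adverse events.** Section 8.9.4 lists what need not be reported as an AE: "Events including withdrawal (except for precipitated withdrawal), injection site reactions, assessments for suicide risk" and further items. Section 14.24.1 gives the list without the exception: "Events including withdrawal, injection site reactions, assessments for suicide risk, overdose and vital signs do not need to be reported as Adverse Events".

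**Analysis.** SAP 8.2.4 says: "A table summarizing the number of participants experiencing a precipitated withdrawal as well as the number of such withdrawals will be generated by treatment arm". It gives no definition, window or denominator.

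**The concern.** Precipitated withdrawal is the only criterion in the RCT pausing rules. A rule of that kind works on the count at the time, so everyone feeding it should be looking for the same event over the same period. Here a site following 8.4.11 must assess rises in the first hour. A site following 8.4.9 is sent to a 4-hour definition that outlasts the RCT's own observation period. The trigger fits the ancillary study, where everyone starts below 8, and is unclear for someone who is already above 12 at entry.

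At stake are the consistency of the pausing count across sites and the meaning of the by-arm safety table. If SL-BUP patients who start at home are included as though they had been watched, the table will show absence of assessment as absence of events.

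**Working it through.** The plan states no event rate or operating characteristic for the pausing rules, so there is no figure to reproduce. The check is textual, followed by an illustration of sensitivity.

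**1. Windows side by side (RCT, XR-BUP arm)**

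| Place | What it governs | Time after injection |
|---|---|---|
| 8.4.11 | Assessment for precipitated withdrawal | 1 h |
| 8.4.9, by reference to 9.8 | Assessment for precipitated withdrawal | 4 h |
| 8.4.9 and 8.9.3 | ED observation | 2 h |
| 8.4.10 | Same COWS threshold, under worsening withdrawal | 2 h |
| 8.4.9, wallet card | Advice to return if the event is suspected | 24 h |
| 8.9.2, 8.4.12, SAP 8.2.4 | Recording, counting, reporting | none stated |

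Take the time at which COWS first exceeds 12. At 45 minutes, 8.4.11 and 9.8 both require assessment. At 90 minutes, 9.8 requires it and 8.4.11 does not, although the patient is still under observation. At 150 minutes, only 9.8 requires it, and the RCT's 2-hour observation is over.

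**2. The trigger for high entry scores**

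Let b be the pre-injection score and f a later score. Reading A (crossing the threshold) requires b ≤ 12 and f > 12. Reading B (any rise ending above it) requires f > b and f > 12.

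| b to f | Reading A | Reading B |
|---|---|---|
| 6 to 14 | met | met |
| 13 to 14 | not met | met |
| 14 to 22 | not met | met |
| 18 to 18 | not met | not met |

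For b of 13 or more, A is never met, while B is met by a one-point rise. The text does not choose between them.

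**3. Sensitivity of the pausing rules to the count**

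The true RCT rate is not given. The rates p below are assumptions. The formula is P(X ≥ k) = 1 − Σ C(n, j) p^j (1 − p)^(n − j), summed over j = 0 to k − 1. The limit of 8 in the first 100 can be read as 8 or more, or as more than 8, so both are shown. Site rule at 3%: 1 − 0.97^5 − 5 × 0.03 × 0.97^4 = 1 − 0.8587 − 0.1328 = 0.0085.

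| Assumed counted rate | ≥ 8 in 100 | ≥ 9 in 100 | > 1 in 5 at a site |
|---|---|---|---|
| 3% | 1.1% | 0.3% | 0.85% |
| 5% | 12.8% | 6.3% | 2.3% |
| 7% | 40.1% | 26.6% | 4.25% |
| 10% | 79.4% | 67.9% | 8.2% |

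If one window yielded a counted rate of 3% and a wider one 7%, the chance of reaching 8 in the first 100 would move from 1.1% to 40.1%. If no events occur after the first hour, the choice of window changes nothing.

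**4. By-arm table**

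Section 8.4.11 covers XR-BUP only, and no SL-BUP trigger or observation period is given. Under 8.4.9, SL-BUP patients with COWS 4 to 7 induce at home. SAP 6.2.1 counts a home induction dose as exposure, and the safety population in SAP 3.2.1.3 is everyone who received treatment. Unless stated otherwise, these participants enter the denominator without having been observed.

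**5. After discharge**

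Table 2 schedules the precipitated-withdrawal form at enrollment only. Later events would have to reach the data through AE reporting, where 8.9.4 and 14.24.1 disagree, or through ED visit data.

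**The case against.** The strongest reply is that the COWS rule triggers an assessment and does not define the event. The event is a clinical determination, 8.9.2 has no threshold or window, and 8.4.12.2 counts any case at any site. Nothing bars a clinician from recording a case outside the trigger. The windows are nested, the clinical criteria in 8.4.11 and 9.8 are the same, and the recorded time lets recorded events be tabulated under any window later. The pointer to 9.8 may be no more than a stale cross-reference, and the component-specific manuals mentioned in Section 13.0 may already settle practice.

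Most of that stands and limits the point. What remains is that the trigger decides which patients the protocol requires to be assessed. Re-counting by time works only for events that were assessed and recorded, and it cannot repair a pausing decision already made on the running count.

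On capture, the ED Visits and Hospitalizations form covers visits to day 30 by patient report and record query, SAP 8.2.8 tabulates and lists them, and the RCT-specific 8.9.4 makes the event AE-reportable to day 30. Post-discharge events are therefore not lost. They are simply not linked to the precipitated-withdrawal table. SAP 8.2.4 is also descriptive, and no comparative test is planned.

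A reader might infer that entrants above 12 can never be counted, or that a 90-minute event is excluded from pausing. The first holds only under reading A. The second does not follow, because 8.4.10 concerns additional medication and does not classify the event.

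**Conclusion.** The passages contradict one another and need reconciling. For the same RCT patients the protocol gives a 1-hour assessment window, a 4-hour one by reference, and 2 hours of observation. The trigger is ambiguous for entry COWS above 12. The pausing rules and SAP 8.2.4 name no window, so the real-time pausing count can depend on the section a site follows. The two AE sections disagree, and the by-arm table lacks a rule for unobserved participants.

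The size of the effect cannot be derived from the documents. The pausing probabilities above rest on assumed rates and show only that the rules are sensitive to the count.

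Two stronger readings are tempting and unsupported. One treats time fractions as a loss of events: the first hour is 1/2 = 50% of the observation period, and (24 − 1)/24 = 96% of the wallet-card period lies beyond it. These are fractions of clock time. The determination turns on rapid onset, and the wallet card is care-seeking advice. Section 3.1 does say "The median time to peak concentration is 24 hours versus about 2.5 hours for SL-BUP", but it adds that buprenorphine is quickly detectable in serum after XR-BUP, so the timing of events cannot be read from the peak. The other reading puts the undercount at 20 to 40% because of high entry scores. That needs reading A, an assumed share of such entrants, and equal risk at every baseline score; the documents support none of these.

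Precipitated withdrawal is the only criterion in 8.4.12, but it is not the only route to a stop. The DSMB (14.23) and the sponsor and FDA (18.0) can act independently.

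**What to change.** 1. Reconcile 8.4.9, 8.4.11 and 9.8 to one RCT definition and window, and state how it applies to patients entering with COWS above 12. The clinical rule is the sponsor's to set.
2. Cite that definition in 8.4.12 and in SAP 8.2.4, so that the pausing count and the table use the same event.
3. Reconcile 8.9.4 with 14.24.1 on whether precipitated withdrawal is AE-reportable.
4. In SAP 8.2.4, report participants dosed and observed in the ED separately and show home-induction participants as not assessed. Tabulate ED returns within 24 hours for suspected precipitated withdrawal from the existing ED visit data, as protocol 12.6.6 already does for the ancillary study.

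The cost is a protocol clarification and SAP wording; the forms already exist. SAP Exhibit 5 reserves version 4.0 for finalizing the RCT sections before database lock, which suits the SAP part. There are two consequences to accept. The reported XR-BUP count may be somewhat higher, and the sponsor should confirm that the existing pausing thresholds still fit the reconciled definition.
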